#### Exclusion criteria

Presence of acute infection in the preceding 7 days or presence of a temperature ≥38.0 °C (oral temperature assessment), or acute symptoms greater than “mild” severity on the scheduled date of first vaccination.History of severe drug and/or food allergies and/or known allergies to the trial product or its components.Any condition that, in the opinion of the investigator, would complicate or compromise the study or wellbeing of the subject.Woman who are pregnant or breast feeding.History or presence of cardiovascular, respiratory, hepatic, renal, gastrointestinal, neuropsychiatric, or immunosuppressive disorders that would be a risk factor when administering the investigational product.History of thymus gland disease.Diagnosed with cancer or receiving treatment for cancer within the 3 years prior to the screening.Evidence of clinically significant anemia and other any significant active hematological disease, or having donated >450 mL blood within the past 3 months.Evidence of substance abuse, or previous substance abuse.Participation in a study involving administration of an investigational compound within the past 4 months, or planned participation during the duration of this study.Administration of any licensed vaccine, such as MMR and/or chickenpox immunization within 30 days before the first study vaccine dose.

#### Premature withdrawal of patients from study

Participants are free to withdraw consent and discontinue participation at any time without penalty and are not obliged to give a reason. Subjects may be withdrawn/removed, if necessary, to protect their health or the integrity of the study. The investigator also has the right to withdraw participants from the study in the event of inter-current illness, adverse events, treatment failures, protocol violations, administrative, or other reasons. When a subject withdraws from the study, all safety data normally required at the completion of the study will be obtained, where possible. All details available will be reported and recorded for any subject that withdraws or is removed from the study.

The Principal Investigator and/or the Sponsor of this study may stop a subject’s participation in the study at any time for one or more of the following reasons:Failure to follow the instructions of the Principal Investigator and/or study staff.The Principal Investigator decides that continuing participation could be harmful.Treatment is needed that is not allowed in the study.The study is cancelled.Other administrative reasons.Unanticipated circumstances.

### Dosing regimen

The dosing regimen is shown in Figure 1.

**Figure 1 Fig1:**
[figure not shown]
Dosing regimen. DENV, dengue virus; JE, Japanese encephalitis; YF, yellow fever.

### Methods and assessments

Subjects will be recruited via the Singhealth IMU healthy volunteer database. Eligible subjects will be approached and invited for participation. The participants will be given the participant information sheet and allowed to ask any questions about the trial. The Principal Investigator or a Co-investigator will take informed consent. Participants meeting all inclusion criteria and no exclusion criteria and who agree to participate will be enrolled and randomized at the IMU.

#### Visit 1 – screening for all groups

Screening procedures will commence once a subject has given informed consent. A physical examination and blood samples will be taken for baseline assessments: dengue immunoglobulin G specific for previous dengue infection, and hematology for full blood count and clinical chemistry (liver and renal panel). Urine will be collected for a pregnancy test (for female subjects of child-bearing potential only).

The study screening procedure is for all subjects, regardless of their randomized group:Informed consentPhysical examinationUrine pregnancy test if applicableSafety bloods which include:Full Blood Count (FBC)Dengue IgGLiver panelRenal panel

Subjects must receive the first dose of vaccination within 21 days of the screening visit.

#### Procedures for groups 1, 2 and 3

The following procedures for subjects randomized to groups 1, 2 and 3 are conducted at the following visits.

#### Visit 2 – dose 1 (Japanese encephalitis)

Pre-dose vital signsUrine pregnancy test if applicableJE vaccination1 hour post-dose physical examination1 hour post-dose vital signs

#### Visit 3 – dose 2 (Japanese encephalitis)

This visit will occur 1 month after the first JE vaccination.Pre-dose vital signsJE vaccination1 hour post-dose physical examination1 hour post-dose vital signs

#### Visit 4 – dose 3 (yellow fever)

This visit will occur 1 month after the second JE vaccination for subjects randomized to group 1, 4 months after the second JE vaccination for subjects randomized to group 2, or 9 months after the second JE vaccination for subjects randomized to group 3.Pre-dose vital signsPre-dose research blood for YF antibody immune response and RNAYF vaccination1 hour post-dose vital signs1 hour post-dose physical examination

#### Visit 5 – 1 day after yellow fever vaccination

Vital signsPhysical examinationResearch blood for YF antibody immune response and RNAAssessment of clinical symptoms

#### Visit 6 – 3 days (+1 day) after yellow fever vaccination

Vital signsPhysical examinationResearch blood for YF antibody immune response and RNAAssessment of clinical symptoms

#### Visit 7 – 1 week (±2 days) after yellow fever vaccination

Vital signsPhysical examinationResearch blood for YF antibody immune responseAssessment of clinical symptoms

#### Visit 8 – 15 days (+2 days) after yellow fever vaccination

Vital signsPhysical examinationAssessment of clinical symptomsReview subject diaryReview adverse events and concomitant medications

#### Visit 9 – 1 month (±5 days) after yellow fever vaccination

Vital signsPhysical examinationResearch blood for YF antibody immune response

#### Visit 10 – 6 months (±14 days) after yellow fever vaccination

Vital signsPhysical examinationResearch blood for YF antibody immune response

#### Procedures for group 4

The following procedures for subjects randomized to group 4 are conducted at these visits.

#### Visit 2 – Dose 1 (yellow fever)

Pre-dose vital signsUrine pregnancy test if applicablePre-dose research blood for YF antibody immune response and RNAYF vaccination1 hour post-dose vital signs1 hour post-dose physical examination

#### Visit 3 – 1 day after yellow fever vaccination

Vital signsPhysical examinationResearch blood for YF antibody immune response and RNAAssessment of clinical symptoms

#### Visit 4 – 3 days (+1 day) after yellow fever vaccination

Vital signsPhysical examinationResearch blood for YF antibody immune response and RNAAssessment of clinical symptoms

#### Visit 5 – 1 week (±2 days) after yellow fever vaccination

Vital signsPhysical examinationResearch blood for YF antibody immune responseAssessment of clinical symptoms

#### Visit 6 – 15 days (+2 days) after yellow fever vaccination

Vital signsPhysical examinationAssessment of clinical symptomsReview subject diaryReview adverse events and concomitant medications

#### Visit 7 – 1 month (±5 days) after yellow fever vaccination

Vital signsPhysical examinationResearch blood for YF antibody immune response

#### Visit 8 – 6 months (±14 days) after yellow fever vaccination

Vital signsPhysical examinationResearch blood for YF antibody immune response

#### Further assessments

During each study visit, subjects will document all symptoms they may experience after the vaccination with YF vaccine. These assessments include local symptoms as well as systemic symptoms. Investigators will check on the presence of fever, nausea, vomiting and myalgia at each point at day 1, day 3, week 1 and day 15. Patients will be monitored again at month 1 and month 6. The patient and their diary will be assessed and reviewed by the investigators to ensure that there are no other symptoms experienced by the subjects. Subjects will be trained to watch out for important clinical signs and symptoms and any unusual manifestations such as high fever, unusual behavior, fits, yellowing of skin and eyes, or any signs and symptoms of a serious allergic reaction such as difficulty breathing, hoarseness or wheezing, hives, paleness, weakness, a fast heart beat or dizziness. They will be educated to inform the study site personnel and the Principal Investigator should any of them develop any of these features.

YF neutralizing antibody titer will be measured using a plaque reduction neutralization test against the vaccine strain YF17D. Innate immune response will be characterized genetically using either microarray or digital PCR (or both). The innate immune response will also be characterized at the protein and metabolite level using Luminex bead technology and lipidomic/metabolomic approaches.

Schematic diagrams of the study assessments are show in Tables 2, 3, 4 and 5.

**Table 2 Tab2:** **Study schema for study arms 1, 2 and 3**

	**Visit 1 screening (-21 to -1 days)**	**Visit 2 - first vaccination (day 0)**		**Visit 3 - second vaccination (+2 weeks from first vaccination)***		**Visit 4 - third vaccination (+2 weeks from second vaccination)***	
		**Pre-vaccination**	**1 hour post-vaccination**	**Pre-vaccination**	**1 hour post-vaccination**	**Pre-vaccination**	**1 hour post-vaccination**
Inform consent	×						
Medical history and demographics	×						
Physical examination	×	x	x	x	x		×
Vital signs^a^	×	×	×	×	×	×	×
Hematology labs^b^	×						
Chemistry labs (liver, renal panel^c^)	×						
Dengue immunoglobulinG^d^	×						
Urine pregnancy test^e^	×	×					
Adverse events^f^	×	×		×		×	
Concomitant medications	×	×		×		×	
Blood sampling in relation to YF17D vaccination						×^g^	

*Window period: for second vaccination is +2 weeks (vaccination cannot be done earlier); for third vaccination (group 1, 2, 3) is +2 weeks (vaccination cannot be done earlier). ^a^Vital signs include temperature (oral and tympanic allowed), blood pressure, pulse rate, and respiratory rate. ^b^Hematology labs include hemoglobin, red blood cell, white blood cell, hematocrit, platelet count, neutrophil, lymphocyte, monocyte, eosinophil, basophil. ^c^Liver panel includes total protein, albumin, total bilirubin, alkaline phosphatase, ALT alanine transaminase, AST aspartate transaminase, gamma-glutamyl transpeptidase. Renal panel includes urea, sodium, potassium, chloride, bicarbonate, creatinine. ^d^Dengue immunoglobulin G will be tested by enzyme-linked immunosorbent assay. ^e^For females only. ^f^Clinical Trial Certificate Adverse Events version 4.0 will be used for grading. ^g^For third vaccination, pre-dose blood sample can be taken any time before dosing. YF, yellow fever.

**Table 3 Tab3:** **Blood sampling schedule for study arms 1, 2, 3**

	**Visit 4**		**Visit 5 - 1 day after**	**Visit 6 - 3 days after (+1 day)**	**Visit 7 - 1 week after (±2 days)**	**Visit 8 - 15 days after (+2 days)**	**Visit 9 - 1 month after (±5 days)**	**Visit 10 - 6 months after (±14 days)**
	**Pre-vaccination (any time before dosing)**	**Post-vaccination (1 hour)**						
Physical examination		×	×	×	×	x	×	×
Vital signs^a^	×	×	×	×	×	x	×	×
Assessment for clinical symptoms (local and general symptoms)		×	×	×	×	x		
Blood sampling in relation to YF17D vaccination	×		×	×	×		×	×
Adverse events^b^	×		×	×	×	x	×	×
Concomitant medications	×		×	×	×	x	×	×

^a^Vital signs include temperature (oral and tympanic allowed), blood pressure, pulse rate, and respiratory rate. ^b^Clinical Trial Certificate Adverse Events version 4.0 will be used for grading. YF, yellow fever.

**Table 4 Tab4:** **Schedule in relation to YF17D vaccination**

	**Visit 4**		**Visit 5 - 1 day after**	**Visit 6 - 3 days after (±1 day)**	**Visit 7 - 1 week after (±2 days)**	**Visit 8 - 1 month after (±5 days)**	**Visit 9 - 1 year after (±7 days)**
	**Pre-vaccination (any time before dosing)**	**Post-vaccination (1 hour)**					
Physical examination		×	×	×	×	×	×
Vital signs^a^	×	×	×	×	×	×	×
Assessment for clinical symptoms (local and general symptoms)		×	×	×	×	×	
Blood sampling in relation to YF17D vaccination	×		×	×	×	×	×
Adverse events^b^	×		×	×	×	×	×
Concomitant medications	×		×	×	×	×	×

^a^Vital signs include temperature (oral and tympanic allowed), blood pressure, pulse rate, and respiratory rate. ^b^Clinical Trial Certificate Adverse Events version 4.0 will be used for grading. YF, yellow fever.

**Table 5 Tab5:** **Study schema for study group 4**

	**Visit 1 – screening (-21 to -1 days)**	**Visit 2 - first vaccination (day 0)**		**Visit 3 - 1 day after**	**Visit 4 - 3 days after (+1 day)**	**Visit 5 - 1 week after (±2 days)**	**Visit 6 - 15 days after (+2 days)**	**Visit 7 - 1 month after (±5 days)**	**Visit 8 - 6 months after (±14 days)**
		**Pre-vaccination**	**Post-vaccination (1 hour)**						
Inform consent	×								
Medical history and demographics	×								
Physical examination	×		×	×	×	×	x	×	×
Vital signs^a^	×	×	×	×	×	×	x	×	×
Haematology labs^b^	×								
Chemistry labs (liver, renal panel^c^)	×								
Dengue immunoglobulin G^d^	×								
Urine pregnancy test^e^	×	×							
Adverse events^f^	×	×		×			x		
Concomitant medications	×	×		×			x		
Blood sampling in relation to YF17D vaccination		×^g^		×	×	×		×	×
Assessment for clinical symptoms (local and general symptoms)			×	×	×	×	x		

^a^Vital signs include temperature (oral and tympanic allowed), blood pressure, pulse rate, and respiratory rate. ^b^Hematology labs include hemoglobin, red blood cell, white blood cell, hematocrit, platelet count, neutrophil, lymphocyte, monocyte, eosinophil, basophil. ^c^Liver panel includes total protein, albumin, total bilirubin, alkaline phosphatase, ALT alanine transaminase, AST aspartate transaminase, gamma-glutamyl transpeptidase. Renal panel includes urea, sodium, potassium, chloride, bicarbonate, creatinine. ^d^Dengue immunoglobulin G will be tested by enzyme-linked immunosorbent assay. ^e^For females only. ^f^Clinical Trial Certificate Adverse Events version 4.0 will be used for grading. ^g^For third vaccination, pre-dose blood sample can be taken any time before dosing. YF, yellow fever.

#### Sample size calculation and statistical analysis

The main analysis will be comparisons between each of the JE groups and the no JE group. To allow for the risk of inflated type 1 error rate, a Bonferroni-type adjustment will be used. A sample size of 21 per group gives 80% power (5%/3 = 1.7% two-sided type 1 error) to detect a difference of 1 unit of log(2)-transformed antibody titer between two groups, assuming the standard deviation is 1 on the log(2) scale. We anticipate a drop-out rate of approximately 20%. However, given the long duration between JE and YF vaccination in group 3 of the JE vaccination arm a higher loss to follow-up rate could occur in this group. Given that group 2 in the JE vaccination arm serves as an intermediate while the largest difference in YF antibody titers is hypothesized to be in groups 1 and 3 in the JE vaccination arm, we weighted each arm differently. Consequently, n = 25 in the YF control arm, n = 25 for the group that receives YF vaccination 1 month after JE vaccination, n = 22 for the group that receives YF vaccination 4 months after JE vaccination, and n = 28 for the group that receives YF vaccination 9 months after JE vaccination. The total number of participants is therefore 100.

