**Table 1 Tab1:** **Study design**

**Groups**	**Vaccination schedule**		
	**1st vaccination (month 1)**	**2nd vaccination (month 2)**	**3rd vaccination**
Group 1	JE vaccination	JE vaccination	Yellow fever vaccination 1 month after second JE vaccine
Group 2	JE vaccination	JE vaccination	Yellow fever vaccination 4 months after second JE vaccine
Group 3	JE vaccination	JE vaccination	Yellow fever vaccination 9 months after second JE vaccine
Group 4	Yellow fever vaccination	No vaccination	No vaccination

JE, Japanese encephalitis.

A total of 100 healthy adults, pre-screened to be negative for anti-dengue antibodies, will be enrolled upon written informed consent; 75 subjects in the test arm will receive two doses of inactivated JE vaccine (Ixiaro, Novartis (Singapore) Pte Ltd, Pharmaceutical Division [name]), while 25 subjects in the control arm will receive no JE vaccination.

Subjects in the test arm will be sub-divided into three groups who receive YF17D (Stamaril, SANOFI PASTEUR SA [name]): group 1, YF vaccination 1 month post-JE vaccination; group 2, YF vaccination 4 months post-JE vaccination; group 3, YF vaccination 9 months post-JE vaccination. Subjects in the control arm (group 4) will receive YF vaccination at month 1.

Blood sampling in relation to YF17D vaccination will take place: 1) pre-dose; 2) 1 day post-dose; 3) 3 days post-dose (+1 day); 4) 1 week post-dose (±2 days); 5) 1 month post-dose (±5 days); and 6) 6 months post-dose (±14 days).

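### The Bonferroni-type 5%/3 split is valid but conservative; naming step-down Dunnett or Holm, and one titer time, would keep the 5% guarantee with power that is never lower

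*Protocol article*

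**What the plan says.** All of the following is in the protocol article, mostly under *Sample size calculation and statistical analysis*.

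- Comparisons: "The main analysis will be comparisons between each of the JE groups and the no JE group". That makes three contrasts, all against group 4.
- Multiplicity: "To allow for the risk of inflated type 1 error rate, a Bonferroni-type adjustment will be used". Whether this is single-step or sequential is not stated.
- Planning level: "A sample size of 21 per group gives 80% power (5%/3 = 1.7% two-sided type 1 error". The target effect and its spread follow in the same sentence: a difference of one doubling in titer, and for the variability, "assuming the standard deviation is 1 on the log(2) scale".
- Losses, in per cent: "We anticipate a drop-out rate of approximately 20". Allocation: "n = 25 in the YF control arm, n = 25 for the group that receives YF vaccination 1 month after JE vaccination", with 22 in the 4-month group and 28 in the 9-month group.
- Sampling, in the text under Table 1: "Blood sampling in relation to YF17D vaccination will take place: 1) pre-dose; 2) 1 day post-dose", and four later draws at day 3, week 1, month 1 and month 6. The visit lists label each of these five post-dose draws for YF antibody response. The sample size section speaks of antibody titer without a time.

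**The concern.** Two things are left open in a sentence meant to fix the main test.

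First, the three contrasts share the group 4 mean, so they are positively correlated. A single-step 5%/3 test ignores this, and it also does not relax the threshold after a first rejection. Procedures with the same 5% guarantee do better. This matters in a trial of 100 people where the stated drop-out takes three of the four groups slightly below the planned 21.

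Second, a divisor of 3 counts group contrasts at a single time. The time to which the family refers is not named, so the scope of the 5% guarantee cannot be read from the text.

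**Working it through.** **1. The plan's own figure.** Inputs: difference δ = 1, SD σ = 1, two-sided α = 0.05/3 = 0.01667, power 80%. With the normal approximation,

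n = 2(z₁₋α/₂ + z₁₋β)² σ²/δ² = 2(2.394 + 0.842)² = 20.94, rounded up to 21.

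The stated 21 per group reproduces, with power 80.1%. With a t reference at 21 per group, power is 76.7% for separate two-sample tests and 78.5% with the four-group pooled variance (80 df).

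**2. Evaluable numbers after 20% loss.** Control 25 × 0.8 = 20; group 1, 25 × 0.8 = 20; group 2, 22 × 0.8 = 17.6, taken as 18; group 3, 28 × 0.8 = 22.4, taken as 22. Error df = 20 + 20 + 18 + 22 − 4 = 76.

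**3. Critical values for |t| at 76 df**, from the largest to the smallest statistic:

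| Procedure | Largest | Second | Smallest |
|---|---|---|---|
| Bonferroni, single-step | 2.448 | 2.448 | 2.448 |
| Holm | 2.448 | 2.287 | 1.992 |
| Step-down Dunnett | 2.398 | 2.255 | 1.992 |

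No step-down value exceeds the Bonferroni value. Every Bonferroni rejection is therefore also a Holm and a step-down Dunnett rejection, and power cannot be lower.

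**4. Family-wise error with no true differences** (simulation, shared control, pooled variance): Bonferroni 4.4%, Holm 4.4%, step-down Dunnett 5.0%. With groups 1 and 3 truly different, the false rejection rate for group 2 is 1.7% under Bonferroni, 4.0% under Holm and 4.1% under step-down Dunnett. The step-down tests use more of the allowed error but stay within 5%.

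**5. Power at 20/18/22 against 20.** The standardized difference is 1/√(1/20 + 1/n): 3.162 for n = 20, 3.078 for n = 18 and 3.237 for n = 22. Simulated power, pooled variance in every column:

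| True differences (groups 1/2/3) | Result | Bonferroni | Holm | Step-down Dunnett |
|---|---|---|---|---|
| 1/1/1 | group 1 | 76.0% | 83.1% | 83.8% |
| | group 2 | 73.4% | 81.5% | 82.2% |
| | group 3 | 78.3% | 84.5% | 85.2% |
| | all three shown | 55.3% | 72.2% | 72.5% |
| 1/0/1 | group 1 | 76.2% | 79.4% | 80.5% |
| | group 3 | 78.2% | 81.0% | 82.1% |
| 1/0/0 | group 1 | 76.1% | 76.2% | 77.8% |

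All columns use the same pooled variance, so the gain comes from the testing procedure and not from pooling. With no losses (25/22/28 against 25) and all differences 1, Bonferroni gives 86.3/83.5/88.3% and step-down Dunnett about 91.8/90.4/93.0%.

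**6. What the divisor covers.** Three contrasts at five times would be 15 tests. At 5%/3 each, the Bonferroni bound on family-wise error is 15 × 0.05/3 = 25%. The correlation of titers across times is not given. For assumed values of 0, 0.5, 0.7, 0.9 and 1, simulation with the shared control gives 20.4%, 17.0%, 14.0%, 9.6% and 4.5%. These figures describe a case that the article does not announce.

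**The case against.** Dividing 5% by 3 for three comparisons is correct and holds the error rate, and the sample size built on it reproduces. The wording may already include Holm, which is a sequential Bonferroni method whose first step is 5%/3, so planning at that level does not exclude it. A condensed article can leave the procedure to the analysis plan, which is not shown. All of this stands. The point is therefore an improvement in efficiency and clarity, and not the correction of an error.

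The power gain also depends on the pattern of effects. The article calls group 2 an intermediate and expects the largest titer differences to involve groups 1 and 3, so three equal differences are the favourable case. A reader might infer that a step-down test always makes up for drop-out. It does not: with one true difference Holm adds 0.1 points. Nor do all groups fall below 21, since group 3 keeps about 22.

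A reader might also infer that the 5% is already lost across five sampling times. The documents do not support that. They list blood draws, not tests, and nowhere say that several times will be main analyses or that the time will be picked after the data are seen.

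**Conclusion.** The point holds as a low-cost improvement. If the adjustment is applied as single-step Bonferroni, it spends about 4.4% of the allowed 5%, and a step-down procedure gives power that is never lower. At the evaluable numbers implied by 20% drop-out, the gain per comparison is:

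- about 6 to 9 points if all three differences are 1 log2 unit, with power to show all three rising from 55% to 72%;
- about 3 points (Holm) to 4 points (step-down Dunnett) if two are real;
- about 0 (Holm) to 1.6 points (step-down Dunnett) if one is.

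These figures assume normal log2 titers, a common SD of 1 and losses of 20% in every group. The missing time point is a supporting clarification: inflation is conditional, and its size rests on assumed correlations.

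**What to change.** State that the three JE-group versus no-JE contrasts, taken from one linear model of log2 YF titer with pooled variance, will be tested by step-down Dunnett at a two-sided family-wise 5%. Holm is the simpler alternative, and it can also be used with unequal-variance tests if a common SD is doubted. Keep 5%/3 as the conservative planning level, so that the sample size text need not change.

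In the same sentence, name the one post-vaccination titer time that this family covers and make the other times secondary. The article gives no basis for preferring one time, so the trial team should choose it on immunological grounds before any titer results are seen.

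The cost is wording only, with no change to numbers, visits or vaccination. The small downside is that simultaneous intervals, such as single-step Dunnett intervals, may not match the step-down decisions exactly. The plan should say that the test governs the conclusion.

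### The enrolled numbers do not carry the required 21 per group through the plan's own 20% drop-out, so power is about 78%, 75% and 80% by its own formula, and the plan does not say so

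*Protocol article*

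**What the plan says.** Everything on this point is in the Protocol article, section Sample size calculation and statistical analysis.

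- Main analysis: "The main analysis will be comparisons between each of the JE groups and the no JE group". That makes three comparisons, all sharing the same control arm.
- Size and power: "A sample size of 21 per group gives 80% power (5%/3 = 1.7% two-sided type 1 error) to detect a difference of 1 unit". The unit is one doubling of titer (log2 scale), and the SD on that scale is taken to be 1.
- Loss: "We anticipate a drop-out rate of approximately 20" per cent. Of group 3, with its long gap between vaccines, the section adds that "a higher loss to follow-up rate could occur in this group"; it gives no figure.
- Allocation: 25 in control, 25 in group 1, "n = 22 for the group that receives YF vaccination 4 months after JE vaccination" (group 2) and 28 in group 3, 100 in total. The unequal weights are explained by group 2 being an intermediate and by groups 1 and 3 being where the largest difference in titers is expected.

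The section names no test and gives no power for the numbers actually enrolled.

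**The concern.** The section sets a requirement (21 per group), a loss rate (about 20%) and an enrolment, and the three do not fit together. Enrolment in three of the four groups is too small to leave 21 after the expected loss. One of these is the control, which enters every main comparison, so its shortfall affects all three.

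The only power figure a reader finds is 80%, and it will naturally be attached to each main comparison. For group 2 in particular, a non-significant result would be credited with more sensitivity than the enrolled numbers give. Group 2 is one of the main comparisons and has the same share of alpha as the others, although it is the smallest group.

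**Working it through.** **Inputs**, all from the sample size section: difference δ = 1 and SD σ = 1 (log2 scale); two-sided α = 0.05/3 = 0.01667; power 80%; loss 20%; enrolment 25, 25, 22 and 28. Assumption: the 20% applies equally to every group.

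**1. Reproduce the plan's figure.** Normal approximation, with z(1−α/2) = 2.394 and z(0.80) = 0.842:

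n = 2σ²(2.394 + 0.842)²/δ² = 20.94, so 21 per group. Power at 21 v 21 is 80.1%. The stated figure reproduces, so the plan used the normal formula.

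**2. Apply the plan's own loss.**

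| Group | Enrolled | After 20% loss | Loss at which 21 remain |
|---|---|---|---|
| Control | 25 | 20 | 1 − 21/25 = 16% |
| Group 1 | 25 | 20 | 16% |
| Group 2 | 22 | 17.6 | 1 − 21/22 = 4.5% |
| Group 3 | 28 | 22.4 | 1 − 21/28 = 25% |

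Keeping 21 after 20% loss needs 21/0.8 = 26.25, so 27 per group.

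**3. Power against control by the plan's formula.** Power = Φ(δ/SE − 2.394), with SE = σ√(1/n + 1/20):

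- Group 1 (20 v 20): SE 0.316; Φ(3.162 − 2.394) = 77.9%
- Group 2 (17.6 v 20): SE 0.327; Φ(3.060 − 2.394) = 74.7%
- Group 3 (22.4 v 20): SE 0.308; Φ(3.251 − 2.394) = 80.4%

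With control at 20, group 3 needs about 22 evaluable subjects for 80%. It falls short once its loss exceeds about 21 to 22% (1 − 22/28 = 21.4%). The plan gives no rate for group 3, so these are assumed values: 79.0% power at 25% loss, 77.4% at 30% and 73.5% at 40%.

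Detectable difference at 80% power, (2.394 + 0.842) × SE: 1.02, 1.06 and 1.00 log2 units for groups 1, 2 and 3.

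**4. A separate matter: the formula.** By the noncentral t distribution, a two-sample t-test has 76.7% power at 21 per group, 79.1% at 22 and 81.2% at 23. So 23 per group are needed to pass 80%, before any drop-out. After 20% loss the t-test gives 74.2%, 70.6% and 77.0%, with detectable differences of 1.06, 1.10 and 1.03 log2 units. If group 3 loses an assumed 30%, its t-test power is 73.6%.

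**The case against.** **The smaller group 2 is deliberate and disclosed.** This stands as an explanation of why group 2 gets fewer subjects. It does not explain group 1, which is named as one of the two groups of greatest interest, or the control: both have 25. Nor does it replace stating what the weighting does to group 2's power.

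**Applying 20% to each group is only one reading.** The rate could be an overall average. If group 3 loses an assumed 30% (8.4 of 28), an overall loss of 20 leaves 11.6 among the other 72, or about 16%. Control and group 1 then keep about 21 each, and power by the plan's formula is about 80%, 77% and 78.5% for groups 1, 2 and 3. The shortfall shrinks to between 0 and 3 points and moves partly to group 3, but does not disappear.

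**Stronger readings that the document does not support.**

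- A reader might infer that drop-out alone takes power to 71–77%. It does not: 3 to 4 points of that come from changing to a t-test, and the section names no test. On the plan's own formula the range is about 75–80%.
- A reader might infer that all three comparisons miss 80%. On the plan's formula group 3 just reaches it at 20% loss (80.4%).
- A reader might infer that the plan claims its allocation preserves 80% power. No such sentence exists. The 80% is attached to 21 per group, where it is correct, and the allocation is described separately.

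**Conclusion.** The point holds as an inconsistency between the required number, the expected loss and the enrolment. With δ = 1, SD = 1, α = 0.05/3 and 20% loss in every group, control, group 1 and group 2 end below the required 21. By the plan's own formula, power falls about 2 points short of 80% for group 1 and about 5 points short for group 2. Group 3 meets 80% with almost no margin, and loses it under the higher loss that the plan itself says is possible.

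That 21 is a normal-approximation figure is an additional and separate point. It costs 3 to 4 further points if the comparisons are made by t-test.

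The shortfall is modest: the difference detectable with 80% power moves from 1 to at most 1.06 log2 units by the plan's formula, or 1.10 by t-test. This is a matter of restating figures and not a design flaw that must be repaired.

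**What to change.** Keep the 100 subjects and the allocation. Add the achieved power to the sample size section, for example:

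> With 100 randomised and 20% drop-out, power to detect 1 log2 unit versus control is about 78%, 75% and 80% for groups 1, 2 and 3 by the normal approximation (74%, 71% and 77% by two-sample t-test); the difference detectable with 80% power is about 1.02, 1.06 and 1.00 log2 units (1.06, 1.10 and 1.03 by t-test).

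Add one sentence saying that the group 2 comparison has lower power because of the weighting, and one saying that group 3 falls below 80% by the normal approximation if its loss exceeds about 21 to 22%. Nothing has to be deleted, since the statement about 21 per group is correct as a normal-approximation figure.

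Cost: wording only. No extra subjects are needed; the stated power becomes slightly less favourable.
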